### Primary endpoint

The primary endpoint of the study is the rate of epidural blood patch within a 15-day follow-up period, that is, the number of patients who receive a blood patch within the 15-day period divided by the total number of participants included.

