### Population

#### Number of patients needed

The sample size calculation is based on a previous study that investigated tetracosactide in PDPH [39] and, retrospectively, on observational data obtained from our hospital database. The primary endpoint is the rate of blood patch in the two groups. We defined the efficacy of tetracosactide as a decrease in blood patch use by 30% in the tetracosactide group, a clinically relevant difference reducing the need for invasive treatment and replacing it with an easily administered treatment that has a known safety profile.

In our centre, 90% of patients with PDPH after epidural analgesia receive a blood patch. The study reported by Hakim [39] found a greater than 50% decrease in PDPH incidence and blood patch use after prophylactic treatment with tetracosactide, in a context of epidural analgesia. We therefore need to include 44 subjects in each group, given a power of 0.80 and type I error of 0.025 (α = 2.5% Fisher’s exact test, power of 80%, p1 = 0.9; p2 = 0.6), to reduce the blood patch requirement by 30%. Thus a total of 88 patients need to be randomised.

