### Randomisation, blinding, and data management

The anaesthesiologist checks the patient’s inclusion criteria and the absence of exclusion criteria. After signing of the informed consent, patients are randomised online using the ClinSight-Online software program (Ennov society, Paris, France). The randomisation list was compiled by a statistician, entered into the software and communicated to the pharmacist to prepare the numbered treatment kits. The randomization is performed by block stratification according to site. Patients are allocated to a treatment number (by the ClinSight software). The study is performed double-blinded; both patients and the medical team are blinded to treatment allocation. An anaesthetic nurse prepares the treatment according to the assigned number to which the rest of the healthcare team is blinded. Patient data are collected on electronic case report forms (eCRFs). The sponsor will independently monitor both locations of this multisite trial every ten patients. This data monitoring is performed by a clinical research associate (CRA). His/her role is to check the consent form, the quality of data collection (missing data, data entry errors …), the availability of treatment at each site, the pharmacy process, and the declaration of any serious adverse event. He/she is employed by the sponsor but is independent of the investigators and is not involved in carrying out the study or interpretation of the results. Anonymized data are only accessible to the investigators, the sponsor, and other authorized persons (statistician, data manager …). They will be stored confidentially for 15 years by the sponsor. They will not be used for further studies without further patient agreement. At the end of the study, we plan to communicate trial results to participants, healthcare professionals and the public via a peer-reviewed publication. Authors will be considered in the case of a substantial contribution to the conception or design of the study or the acquisition, analysis or interpretation of data. They will need to have drafted the work or revised it critically. They will all approve the final version to be published. We do not expect the participation of a professional writer. Data not disclosed in the publication will not be accessible.

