### Statistical analysis

Unblinding occurs at the end of the study and once the database has been frozen. Analyses will be carried out on an intention-to-treat (ITT) basis. If data are missing from visits, we will carry forward the last value for which the pain (and other symptoms) has not improved. This is the most pessimistic scenario for this condition, which usually improves spontaneously. Blood patch can only be performed at the hospital, and it is therefore very unlikely that there will be missing data regarding the primary endpoint. If a patient does not receive full treatment, she will be included in the group to which she was randomised for further ITT analysis. Statistical analyses will be performed using IBM SPSS statistics for windows (IBM corp., Armonk, NY, USA) and R (R Foundation for Statistical Computing, Vienna, Austria). All data will be checked for normal distribution using the Kolmogorov test. For normally distributed data, variables will be presented as mean ± standard deviation (SD). Non-normally distributed data will be presented as the median and interquartile range [IQR]. Categorical variables will be presented as number and percentage of the total. To compare the two groups (tetracosactide and placebo), we will use Fisher’s exact test for qualitative data and the non-parametric Mann-Whitney tests for quantitative variables. A comparison of the two groups at randomisation will identify potential bias due to unequal allocation. A multivariate logistic regression analysis will be performed to study factors independently associated with the response to tetracosactide and to control potential confounding factors.

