## Discussion

We propose herein a protocol to investigate the use of tetracosactide, an ACTH analogue, to treat PDPH. Blood-patch is currently the gold standard for PDPH treatment, and tetracosactide could be interesting as it would reduce the need for the invasive procedure and replace it with an easily administered treatment that has a known safety profile. Given previous results obtained in small groups of patients, evidence for the efficacy of ACTH analogues for PDPH treatment remains limited.

Initially, the inclusion was limited to PDPH due to a dural puncture carried out by a large Tuohy needle. Because patient enrolment/inclusion was more difficult than expected, the protocol was amended to extend inclusion to all postpartum PDPH. This widening of the inclusion criteria raises the issue of population heterogeneity, which we hope to limit by the randomisation process.

Since the management strategy of PDPH (using blood-patch and non-invasive treatments) is not clearly defined, the rate of blood-patch varies. Rucklidge, for example, described that 50 blood-patches were received by 144 patients treated for PDPH after epidural anaesthesia over 20 years in the hospital in which he practiced [47]; the blood-patch rate was therefore 35%. In the study reported by Aya et al. all patients (100%) treated for PDPH after epidural obstetric anaesthesia in their unit received a blood patch [48]. Therefore, a potential limitation of the study described herein is that the sample size could be insufficient if the rate of blood patch in the control group is lower than 90%.

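### The primary Fisher test ignores the site stratum and the puncture type added by amendment; it stays valid, but may lose power and is exposed to chance imbalance

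*Protocol article*

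**What the plan says.** - **Endpoint.** The primary endpoint is a proportion (Primary endpoint): "the number of patients who receive a blood patch within the 15-day period divided by the total number of participants included".
- **Test.** Statistical analysis assigns Fisher's "exact test for qualitative data and the non-parametric Mann-Whitney tests for quantitative variables". The sample size section rests on the same test: Fisher's "exact test, power of 80%, p1 = 0.9; p2 = 0.6", at a type I error of 0.025. Neither section mentions strata or covariates for this comparison.
- **Randomisation.** "The randomization is performed by block stratification according to site". Puncture type is not named as a stratum.
- **Population.** The 90% control rate is the centre's figure for headache after epidural analgesia (Number of patients needed). Protocol amendment then widens entry from large Tuohy needle punctures to 25-27G spinal punctures. Neither the blood patch rate nor the expected share of the added group is given.
- **Heterogeneity.** The Discussion states: "This widening of the inclusion criteria raises the issue of population heterogeneity, which we hope to limit by the randomisation process".
- **Adjustment.** Statistical analysis says "A comparison of the two groups at randomisation will identify potential bias due to unequal allocation". It then plans a multivariable logistic regression, both to "study factors independently associated with the response to tetracosactide" and to control confounding. How this model relates to the primary test is not stated.

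**The concern.** A factor used to stratify the randomisation normally enters the primary analysis, and so does a strong prognostic factor known at baseline. Leaving them out costs power when they predict the outcome. For a factor that is not a stratum, it also leaves the crude difference open to chance imbalance.

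Both factors could plausibly matter here. The 90% rate covers only the epidural group. The decision to give a patch rests partly on the anaesthesiologist's judgement (text following Fig. 2), and the Discussion itself cites patch rates of 35% and 100% from different units. Randomisation balances puncture type only on average and does not make the population less heterogeneous. With 44 per arm the imbalance in a single trial can be sizeable.

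The planned regression does not clearly fill the gap. It has no stated standing beside the primary test. A main effect in such a model shows who receives a patch, whereas factors of response to the drug need an interaction with treatment.

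**Working it through.** **Inputs from the protocol article:** 44 per arm; type I error 0.025; control rate 0.9; tetracosactide rate 0.6; Fisher's exact test; interim after 44 patients.

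**Assumptions, because the documents give no figures:** the share of small-needle spinal patients, their control patch rate, an even split between two sites, 22 per arm at the interim, and one odds ratio across strata. That odds ratio is taken from the plan's own rates: (0.9/0.1) / (0.6/0.4) = 9 / 1.5 = 6.

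**1. The plan's own figure.** Exact enumeration of the two-sided Fisher test at 0.025, 0.9 against 0.6, gives power 0.811 with 44 per arm (0.796 with 42). The stated 44 per arm is reproduced.

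**2. Power at 44 per arm.** Simulation of pooled Fisher against a continuity-corrected CMH test over the four site-by-puncture strata, two-sided 0.025. Large-needle control rate 0.90 throughout.

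| Spinal share | Spinal control rate | Fisher | Stratified |
|---|---|---|---|
| no heterogeneity | 0.90 | 0.81 | 0.80 |
| 30% | 0.60 | 0.82 | 0.85 |
| half | 0.50 | 0.75 | 0.85 |
| 30% | 0.35 | 0.62 | 0.79 |

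The stratified test rejected in about 1% of trials under the null, so its gain is not bought with type I error.

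With puncture type as the only stratum and 30% spinal, the corrected CMH gave 0.85 against 0.85 for a spinal rate of 0.80, and 0.86 against 0.81 for 0.60. At a spinal rate of 0.70 the result depends on the test: no gain with the corrected CMH (0.86 against 0.86), about 4 points with an exact stratified test (0.89 against 0.84).

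**3. Site alone, 22 per site per arm.** Fisher against an exact stratified test: control rates 0.90/0.90, 0.80 and 0.81; 0.95/0.85, 0.75 and 0.78; 0.95/0.60, 0.70 and 0.82.

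**4. Chance imbalance in puncture type.** With half the patients spinal, the SD of the between-arm difference in spinal share is sqrt(0.5 × 0.5 × 2/44) = 0.107. The 95% range is ±1.96 × 0.107 = ±0.21. If patch rates differ by 40 points, the crude treatment difference moves by up to 0.21 × 40 = about 8 points, against 30 sought.

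A milder case is 30% spinal, where a gap of 8 or more patients between arms has probability about 8%. Take 9 against 17 spinal patients. With no drug effect the crude difference shifts by (8/44) × rate gap:
- gap 20 points: 3.6 points
- gap 40 points: 7.3 points
- gap 55 points: 10.0 points

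With a true odds ratio of 6, Fisher's power is 0.94 to 0.96 if that imbalance favours tetracosactide. If it runs the other way, power is 0.71, 0.45 and 0.24 for the three gaps. The exact stratified test stays between 0.81 and 0.88 in all six cases.

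**5. Type I error of Fisher.** Averaged over randomisations it was at most 0.018 against 0.025. Only conditional on the 9-against-17 imbalance, and only for the 40- and 55-point gaps, did it reach 0.03 to 0.04.

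**6. Interim, 22 per arm, puncture type not prognostic.** Fisher 0.43; continuity-corrected CMH over four strata 0.35 to 0.36.

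**7. Room for covariates.** Under the plan's rates, 44 × 0.1 + 44 × 0.4 = 22 patients are expected without a patch. If spinal patients need fewer patches the number rises. With half spinal and control rates 0.90/0.50, the arm averages are 0.70 and 0.371, giving 44 × 0.30 + 44 × 0.629 = about 41.

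**The case against.** An unadjusted primary test beside an adjusted model is a legitimate design, and the Discussion openly discloses both the heterogeneity and the risk that 88 patients are too few. Three stronger readings are tempting, and the documents do not support them.

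- **That Fisher's type I error is inflated.** It is not. The primary test is fixed in advance, a regression run beside it cannot change its error rate, and step 5 shows it to be conservative on average.
- **That adjustment is left to post-hoc baseline comparisons.** A regression to control confounding is planned. The baseline comparison stands next to it in the text, but nothing says that it triggers or selects covariates. Naming covariates is commonly left to an analysis plan, which is not shown here.
- **That power is certainly lost.** The loss depends on rates that the documents do not give, and it vanishes when puncture type is weakly prognostic.

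Two practical objections stand. A continuity-corrected stratified test is weaker than Fisher at the interim if puncture type does not matter. Puncture type is also not always clear: Eligibility admits combined spinal-epidural analgesia, and Intervention protocols covers headache whether or not an accidental puncture was diagnosed.

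None of this removes the core. The primary test is stated, it omits a design stratum, and it omits a factor that the authors themselves flag as a source of heterogeneity.

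**Conclusion.** The point holds as one of efficiency and conditional bias. At 88 patients the unadjusted test loses about nothing if patch rates differ by 10 points or less between puncture types. It loses about 3 to 5 points of power for a 30-point gap with 30% spinal, and about 10 to 17 points for gaps of 40 to 55 points. A plausible chance imbalance can move the crude difference by roughly 4 to 10 points of the 30 sought. These figures assume a common odds ratio of 6, a large-needle control rate of 90%, and spinal shares and rates chosen for illustration. Separately, the planned regression needs a stated role beside the primary test, and its aim of finding factors of response requires an interaction term.

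**What to change.** Amend the analysis text before any unblinding and before the 44-patient interim (Trial status reports 25 enrolled in May 2019):

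1. Make the primary analysis an exact stratified (conditional) test, a CMH test, or a logistic regression, stratified by site and puncture type. Use the same method at the interim and final analyses.
2. Define puncture type with a rule for combined spinal-epidural and unidentified punctures, for example any Tuohy puncture known or suspected against small-needle spinal only. Classify without knowledge of allocation.
3. Report the stratified risk difference with its interval.
4. Keep unadjusted Fisher as a sensitivity analysis.
5. Limit the adjustment covariates to these two factors, and say that the baseline comparison is descriptive.
6. Replace the search for factors of response by one prespecified treatment-by-puncture-type interaction.

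The cost is wording plus the classification of puncture type. If puncture type is not prognostic, about 1 to 2 points of power are given up at 88 patients and, with a continuity-corrected CMH, about 7 to 8 points at the interim. The exact stratified test showed no loss at 88 patients when stratified by site alone with equal rates (0.81 against 0.80); its power at the interim should be checked before choosing.

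### Headache NRS is compared by an unadjusted Mann-Whitney test although an entry NRS is assessed for eligibility: valid, but it gives up precision that costs nothing to recover

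*Protocol article*

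**What the plan says.** Under Secondary endpoints, headache intensity is the score on the 11-point NRS at days 1, 2, 3 and 15. It is a level at each time, not a change from entry. Under Statistical analysis, the two groups are compared with Fisher's exact test for qualitative data and "the non-parametric Mann-Whitney tests for quantitative variables".

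Under Eligibility, the headache must score above 3/10, so on an 11-point scale the entry score lies between 4 and 10. Under Randomisation, blinding, and data management, allocation is blocked and stratified by site.

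The Statistical analysis section uses baseline information or covariates in two other places. The first reads "A comparison of the two groups at randomisation will identify potential bias due to unequal allocation". It looks for imbalance but attaches no adjustment of the NRS comparison to it.

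The second reads "A multivariate logistic regression analysis will be performed to study factors independently associated with the response to tetracosactide". This model, which is also meant to control confounding, is a logistic model for a response whose covariates are not named. It is not a model for the NRS score.

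**The concern.** Among patients with the same complaint, those who start with a worse headache will often score higher a day or two later. If so, part of the spread in follow-up NRS is predictable from the entry score. A two-sample rank test treats that part as noise. A model that includes the entry score removes it and also corrects the estimate for whatever difference in entry NRS arose by chance between arms of 44.

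The stake is the precision of the comparison of headache intensity. The score needed for adjustment must already be assessed to decide eligibility, so the precision could be recovered without more patients or visits.

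**Working it through.** **1. The plan's own figure.** The only sample-size statement concerns the blood patch rate: "We therefore need to include 44 subjects in each group", with "α = 2.5% Fisher’s exact test, power of 80%, p1 = 0.9; p2 = 0.6". Exact enumeration of a two-sided Fisher test at 0.025 gives power 0.796 with 42 per group, 0.811 with 43 and 0.811 with 44. The stated 44 per group (88 in total) therefore reproduces. It says nothing about the NRS, for which no SD, effect size, power or correlation is given. Every NRS figure below rests on assumptions.

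**2. Analytic gain.** Assume a difference that the unadjusted comparison would detect with 80% power at two-sided 5%.

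- Noncentrality without adjustment: 1.960 + 0.842 = 2.802.
- Adjusting for a baseline with correlation rho multiplies the residual variance by 1 − rho².
- Adjusted power = Φ(2.802/√(1 − rho²) − 1.960).
- Equivalent unadjusted total = 88/(1 − rho²).

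| rho | Variance reduction | Adjusted power | Gain (points) | Equivalent total N |
|---|---|---|---|---|
| 0.2 | 4% | 81.6% | 1.6 | 92 |
| 0.3 | 9% | 83.6% | 3.6 | 97 |
| 0.4 | 16% | 86.4% | 6.4 | 105 |
| 0.5 | 25% | 89.9% | 9.9 | 117 |
| 0.6 | 36% | 93.8% | 13.8 | 138 |

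At rho 0.1 the gain is 0.4 points. At a two-sided level of 0.025 the gains for rho 0.2 to 0.6 are 1.7, 3.9, 6.9, 10.6 and 14.7. The starting power also matters: at rho 0.5 and two-sided 5% the gain is 11.9 points from 50% power and 6.3 from 90%.

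**3. Effect of the entry cut on rho.** Restricting entry scores to 4–10 narrows their range and weakens the correlation. For assumed underlying entry distributions with (mean, SD) of (5, 2.5), (6, 2) and (7, 2), a correlation of 0.5 before the cut becomes 0.36, 0.42 and 0.43 after it. Put into the formula above, 0.36 to 0.43 gives a gain of about 5 to 7 points.

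**4. Mann-Whitney against ANCOVA directly.** The formula in step 2 compares two analyses of means, so the test named in the plan was also simulated. Settings: 44 per arm, scores rounded to 0–10, entry scores cut at above 3, follow-up SD 2.5, difference 1.55, two-sided 5%, 2,000 runs per row.

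| Observed rho | Mann-Whitney | ANCOVA |
|---|---|---|
| 0.16 | 79.9% | 81.3% |
| 0.25 | 79.2% | 82.3% |
| 0.41 | 82.2% | 89.8% |
| 0.51 | 82.3% | 93.0% |
| 0.61 | 85.8% | 97.0% |

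The pattern agrees with step 2. With no treatment effect and a correlation of 0.5 before the cut, Mann-Whitney rejected in 5.5% of runs and ANCOVA in 5.7%. The simulation centred placebo follow-up scores near 4, so it does not represent day 15, when many scores may be at or near zero.

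**The case against.** The strongest reply is that nothing here is wrong. In a randomised comparison the unadjusted Mann-Whitney test keeps its type I error, as the null simulation shows. A rank test is a reasonable choice for a bounded score that will pile up at low values: the Background itself reports resolution in more than 70% of patients within a week. The NRS is a secondary endpoint for which no power was planned, so no planned power is lost. All of this stands.

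It can also be said that covariate adjustment of a secondary endpoint belongs in an analysis plan that is not shown. That is only partly an answer, because the article does not leave the method open. It names a test that cannot take a covariate.

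Recording of the numeric entry NRS is inferred. Eligibility shows that it must be assessed, but the schedule figure is not shown.

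Some stronger readings are tempting, and the documents do not support them:

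- **A loss of about 10 points of power.** This needs rho near 0.5 and a starting power near 80%. The article gives neither.
- **Bias from chance differences in entry NRS.** Such differences add noise that the unadjusted test already allows for. They do not bias it systematically.
- **Day 1 NRS as the key symptom result, or as the evidence that fewer patches mean fewer symptoms.** Secondary endpoints ranks no time point above the others. The Abstract and the Conclusion infer fewer symptoms directly from fewer blood patches and do not mention the NRS. Choosing a lead time point would be a separate design preference.

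**Conclusion.** The point holds as a free improvement. The stated comparison of headache NRS leaves out a baseline score that must be assessed for eligibility, and neither the comparison at randomisation nor the logistic model makes up for this.

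The size cannot be fixed from the article. From an assumed 80% power at two-sided 5%, the gain runs from about 2 points at rho 0.2 to about 14 at rho 0.6. Three features of the protocol may push rho towards the lower end: the entry cut, analgesia adjusted daily, and blood patch permitted from 24 h after study treatment. At day 15, with most headaches probably resolved, the gain may be close to zero.

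The planned test is valid, and the primary endpoint, its Fisher test and the total of 88 are not affected.

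**What to change.** In Statistical analysis, state that the NRS at days 1, 2, 3 and 15 will each be compared with a model containing treatment, entry NRS and site. Site belongs in the model because randomisation is stratified by it. ANCOVA is adequate; a proportional-odds model or rank ANCOVA keeps the analysis ordinal if preferred. Report the adjusted difference (or adjusted odds ratio) with its 95% CI, and keep Mann-Whitney as a sensitivity analysis.

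Confirm that the numeric entry NRS is captured in the eCRF, not only the fact that the threshold was met.

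The cost is about one sentence, settled before unblinding. If the entry score is already in the eCRF, as the eligibility criterion suggests, no extra patients, visits or measurements are needed.
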